### Treatments

The trial treatments are a naturally occurring combination of omega-3 s (Lyprinol®/Omega XL), and placebo. Participants must take either 3 × or 4 × 260 mg capsules in the morning (with breakfast). *Principal Ingredients per 260 mg capsule for the tablets are:* Natural mono-unsaturated Olive oil - 100 mg; PCSO-524® GLM pat. lipids (Eicosatetraenoic acid) - 50 mg; and Vitamin E (D-alpha-Tocepherol) as antioxidant - 0.225 mg. The Lyprinol capsules contain 18% EPA (46.8 mg) and 14% DHA (36.4 mg) per capsule. The placebo capsule contains 35.5 mg of olive oil, 112 mg of lecithin, 12 mg of coconut oil and 0.5 mg of 30% beta-carotene. Both treatments are contained within tablets consisting of: Gelatin; Sorbitol syrup; Glycerin. The placebo capsule matches the Lyprinol® capsule in touch, taste, smell and size.

In terms of the PCSO-524® component in each Lyprinol/Omega XL capsule: Lyprinol® is a lipid extract of the New Zealand green lipped mussel (*Perna canaliculus*). Its major active constituents are unsaturated fatty acids. The amount of these fatty acids ranges between 6.3% and 9.5% for the omega-6 class, and between 9.8% and 12.15% for the omega-3 class. Lyprinol/Omega XL is currently listed with the TGA of Australia as an anti-inflammatory. Lyprinol/Omega XL has been shown to be a reproducible, relatively stable, source of bioactive lipids with a much greater potency than plant/marine oils currently used as nutritional supplements to ameliorate signs of inflammation. Experimental studies have shown that lipid extracts are effective at modulating 5’lipoxygenase and cyclo-oxygenase pathways, which are responsible for the production of eiconoids, including leukotrienes and prostaglandins. The lipid extract of the New Zealand green lipped mussel (*Perna canaliculus*), marketed under the brand name Lyprinol and Omega XL, is rich in eicosapentaenoic acid (EPA) and docosahexanoic acid (DHA), omega-3 fatty acids that inhibit the metabolism of arachidonic acid. The compound is a mixture belonging to a lipid group called sterol esters (SE). The fatty acids in the SE fraction are mainly myristic acid, palmitic acid, palmitoleic acid, stearic acid, oleic acid, linoleic acid, EPA and DHA. The sterols found in this fraction included cholesterol, cholesta-3, 5-diene, 26, 27-dinoergostadienol, cholesta-5, 22-dien-3-ol, ergosta-5, 22-dien-3-ol.

### Procedure

Participants will be randomly allocated to a coded treatment group and they will be given a supply of their treatment. Participants will be required to take either 3 or 4 capsules daily (in the morning with breakfast) for the following 14 weeks. The schedule for testing is presented in Table 1. Weight plays a large role in the digestion and absorption of nutrients giving reason for the researcher’s choice of a weight limit (± 45 kg) over that of an age limit in order to determine how many capsules each child would take.

**Table 1 T1:** Behavioural and demographic measures

	**V1**	**V2**		**V3**		**V4**	
	**Week 1**	**Week 2**	**Week 4**	**Week 8**	**Week 10**	**Week 14**	**Week 18**
	**Practice**	**Centre**	**Home**	**Centre**	**Home**	**Centre**	**Home**
Structured Interview	X						
(DSM ADHD Rating)							
Conners’ Parent Rating Scale		X	X	X	X	X	X
Global Clinical Impressions Scale		X		X		X	
Current Health & Medical Questionnaire	X	X	X	X	X	X	
Demographics Questionnaire	X						
Omega-3 Intake/Food Diary	X			X			
***Cognitive and Psychophysiological Measures***							
COMPASS cognitive battery	X	X		X		X	
Test of Variables of Attention (TOVA)	X	X		X		X	
Brunel Mood Scale (BRUMS)	X	X	X	X	X	X	X
EEG Resting State		X		X		X	
Steady State Topography (SST)		X		X		X	

The first centre visit is a practice day where participants complete screening questionnaires and familiarise themselves with the study procedures and tests. The next Centre visit is a baseline session where participants complete all tests (including the EEG) and are randomly allocated to receive one of the two treatments (Lyprinol®/placebo) for the next 14 weeks. Testing for all subsequent centre visits will follow the same outline of their baseline session with follow up visits at weeks 8 and 14. In between these times, in weeks 4 and 10, the parents will complete a CPRS and health questionnaire while the participants will complete a mood questionnaire used in previous visits. As the study progresses researchers will contact the participants to determine compliance rates for the daily use of the intervention as well as any adverse events. Throughout the duration of the study, parents will be required to complete the CPRS at home and bring in the completed questionnaire each session or at the end of the study. The participants will be given a treatment compliance diary and participants will need to mark each day they take their treatment (this is to monitor for compliance). At the end of the study, participants will be required to return the compliance diary and symptom checklists to the researcher as well as any remaining treatment. The parent will also complete a seven-day food diary in order to determine if the child’s omega-3 intake from non-trial sources has remained consistent since visit 1.

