### Post-treatment period: follow up

Participants’ parents will complete the CPRS and the Brunel Mood Scale four weeks following the cessation of Active or placebo administration to determine any changes in mood or behaviour since ceasing treatment. These scales can be completed by the parents independently or (more usually) with the child. Participants will be questioned non-specifically for any Adverse Events (AEs). A review of their Symptom Checklists will also help to determine if a participant experienced an AE. Figure 1 describes the flow of data collection for this study.

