#### Randomization and safety

Randomization of participants to treatment groups will be determined by random allocation. All 150 participants will be assigned to treatment group A or B using a computer generated random number generator by a neutral third party. Eligible, recruited participants will be assigned a participant number. The treatment number that has been placed next to the participant’s number will be the allocated treatment for that individual. Blinding will be achieved by enlisting a person outside of the project to code the treatments, and maintain the key to this code until data collection is completed. An emergency code break envelope will be provided to the principle investigator which will only be opened in case of emergency. Participants’ parents will also be given a weekly symptom checklist to complete to monitor for any adverse events. Researchers will be blinded to the treatment conditions.

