### Global clinical impression scale (GCI)

Amongst the most widely used of extant brief assessment tools in psychiatry, the GCI is a 3-item observer-rated scale that measures illness severity (CGIS), global improvement or change (GCIC) and therapeutic response. The GCI has proved to be a robust measure of efficacy in many clinical drug trials, and is easy and quick to administer. The GCI is rated on a 7-point scale, with the severity of illness scale using a range of responses from 1 (normal) through to 7 (amongst the most severely ill patients). GCIC scores range from 1 (very much improved) through to 7 (very much worse). Treatment response ratings should take account of both therapeutic efficacy and treatment-related adverse events and range from 0 (marked improvement and no side-effects) and 4 (unchanged or worse and side-effects outweigh the therapeutic effects). Each component of the GCI is rated separately; the instrument does not yield a global score.

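### The weekly symptom checklist is meant to monitor adverse events but is due back only at the end of the study; collecting completed forms at the existing week 8 visit would make it usable during treatment

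*Protocol article*

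**What the plan says.** Under Randomization and safety, the protocol article states the purpose and frequency of the form: "parents will also be given a weekly symptom checklist to complete to monitor for any adverse events". The Procedure section, in the text after Table 1, fixes when it comes back: "At the end of the study, participants will be required to return the compliance diary and symptom checklists to the researcher". The section on the post-treatment period adds that "A review of their Symptom Checklists will also help to determine if a participant experienced an AE", without giving a time for that review. No earlier collection or review is described.

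Four other statements bear on the point:

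- **Other adverse event channels.** Procedure says that "researchers will contact the participants to determine compliance rates for the daily use of the intervention as well as any adverse events", with no frequency given. Table 1 schedules a current health and medical questionnaire at weeks 4, 8, 10 and 14, among other times.
- **Another home form.** In the same paragraph, parents may "bring in the completed questionnaire each session or at the end of the study" when the form is the Conners' scale.
- **Clinical rating.** Under Global clinical impression scale, "Treatment response ratings should take account of both therapeutic efficacy and treatment-related adverse events". Table 1 marks this scale at week 8.
- **Duration.** Procedure states: "Participants will be required to take either 3 or 4 capsules daily (in the morning with breakfast) for the following 14 weeks". The week 18 assessment falls "four weeks following the cessation of Active or placebo administration".

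**The concern.** A weekly form helps monitoring only if someone on the study team sees it during the period it covers. Here the return time is stated, and it falls after that period. The weekly entries can then support a retrospective count of adverse events, but on the stated rule they do not inform anyone while the child is still being dosed.

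What is at stake is modest. At week 8 the child attends the centre, has about 6 weeks of capsules left, and receives a global clinical impression rating that should reflect adverse events. A week-by-week written record already exists at home by then but is not due back. The same paragraph lets the Conners' form come in at visits, so handing in home forms at a visit is already part of the design. Sample size, power and the primary analysis are not affected.

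**Working it through.** The plan gives no figure on this point to reproduce. The check is a count of how long each form waits between completion and return.

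**Inputs from the protocol article**

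- One checklist per week (Randomization and safety).
- 14 weeks of capsules (Procedure).
- Centre visits after baseline at weeks 8 and 14 (Procedure, Table 1).
- Follow-up at week 18, four weeks after the last dose (Post-treatment period).

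**Assumptions**

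- One form is completed at the end of each dosing week, and only on-treatment forms are counted.
- The end of the study is not defined for this purpose, so both week 14 and week 18 are shown.
- Weeks are counted in two ways. Counting from first dose fits both 14 weeks of dosing and a week 18 follow-up four weeks after stopping. Table 1 puts baseline at week 2, which leaves 14 − 2 = 12 weeks of dosing to week 14. That does not fit the stated 14, so it is shown only as the alternative count.

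**Formula.** Wait for the form of week k = week of return − k.

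**Forms in hand at week 8 after the change**

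- From first dose: 8 of 14 = 57%, with 14 − 8 = 6 weeks of dosing left.
- Table 1 labels: (8 − 2) of (14 − 2) = 6 of 12 = 50%.

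**End of study = week 14, counted from first dose (forms of weeks 1 to 14)**

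- Now: waits run from 13 down to 0. Longest 13; mean 91/14 = 6.5 weeks.
- With week 8 collection: forms 1 to 8 wait 7 down to 0 (sum 28), and forms 9 to 14 wait 5 down to 0 (sum 15). Longest 7; mean (28 + 15)/14 = 43/14 = 3.1 weeks.

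**End of study = week 14, Table 1 labels (forms of weeks 3 to 14)**

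- Now: waits run from 11 down to 0. Longest 11; mean 66/12 = 5.5 weeks.
- With week 8 collection: forms 3 to 8 sum to 15 and forms 9 to 14 sum to 15. Longest 5; mean 30/12 = 2.5 weeks.

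**End of study = week 18**

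- Now: longest wait is 18 − 1 = 17 weeks from first dose, or 18 − 3 = 15 weeks on Table 1 labels.
- With week 8 collection: the longest wait belongs to the week 9 form, 18 − 9 = 9 weeks, on either count.

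**The case against.** The strongest reply is that adverse events are already sought during treatment. Researchers contact families about them, the health questionnaire is scheduled four times after dosing starts, and two of those times coincide with centre visits. An emergency code break is also in place. This stands, and it limits the point to the checklist itself. A reader might infer from the late return that adverse events go unmonitored until the end, or that the waits above are delays in detecting an event. The document supports neither inference.

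A second reply is that a journal article condenses the full protocol, which may say when the forms are inspected, and that fixing the hand-back does not forbid an earlier look. This stands in part. The article does not say that the forms go unread until the end. But it is not silent on timing either: it states a return time, and that time suits the form's stated purpose poorly.

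A third reply is that the clinical impression rating need not draw on the checklist. That is correct. The health questionnaire falls at the same week 8 visit, and the rater can ask the parent. It would be wrong to infer that the week 8 rating is made without adverse event information, or that it is biased between arms. The rating is only a convenient occasion to use the extra record.

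Finally, late return is tolerated even for the primary outcome form, so it may be a deliberate logistical choice. That explains the rule. It does not make the rule fit a form whose purpose is monitoring, and the Conners' form may at least come in at each session.

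**Conclusion.** The point holds as a minor weakness. The checklist is described as a monitoring tool, but its stated return at the end of the study means that, as written, it does not do that work during treatment. Neither of the other channels gives a week-by-week written record: the contacts have no stated frequency, and the questionnaire is not weekly.

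Collection at week 8 would put about half or slightly more of the forms in the researchers' hands while dosing continues. It would roughly halve the longest wait if the study ends at week 14; if it ends at week 18, the longest wait falls by 8 weeks (6 on Table 1's labels). These figures rest on one form per week and on the two readings of when the study ends. The conclusion is the same on both readings and on both week counts.

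**What to change.** Add one sentence to Procedure, in the paragraph after Table 1: families bring all symptom checklists completed so far to the week 8 visit (V3), where a blinded researcher reviews them for adverse events before the week 8 global clinical impression rating; the remaining checklists are returned at the end of the study as already planned.

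The cost is that sentence and a few minutes of researcher time at V3. No visit, form or member of staff is added.

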### Post-treatment period: follow up

Participants’ parents will complete the CPRS and the Brunel Mood Scale four weeks following the cessation of Active or placebo administration to determine any changes in mood or behaviour since ceasing treatment. These scales can be completed by the parents independently or (more usually) with the child. Participants will be questioned non-specifically for any Adverse Events (AEs). A review of their Symptom Checklists will also help to determine if a participant experienced an AE. Figure 1 describes the flow of data collection for this study.

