### Mood

The Brunel Mood Scale (BRUMS) was derived from the Profile of Mood States mood scale [64] and contains 24 simple mood descriptors such as angry, energetic, nervous, and unhappy. The BRUMS (formerly known as the profile of Mood States – Adolescents or POMS-A) was designed for purely adolescent populations and the validation process can be found in Terry et al [55,65].

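### The mood scale's informant moves from child to parent at week 18, so within-arm mood change after stopping cannot be read; CPRS completion at that visit is also not standardised

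*Protocol article*

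**What the plan says.** **During treatment.** The text after Table 1 in the Procedure section splits the two scales between two informants at weeks 4 and 10: "the parents will complete a CPRS and health questionnaire while the participants will complete a mood questionnaire used in previous visits". At the baseline centre visit the same paragraph has the participants doing every test, and it says that the later centre visits (weeks 8 and 14) follow the baseline outline. Table 1 schedules the BRUMS at all of these visits and at week 18.

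**After treatment.** The section on the post-treatment period states: "Participants’ parents will complete the CPRS and the Brunel Mood Scale four weeks following the cessation of Active or placebo administration". It gives the purpose as finding changes in mood or behaviour since treatment ended. It then adds: "These scales can be completed by the parents independently or (more usually) with the child".

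**The primary outcome.** The Primary outcome section makes the parent the person who fills out the CPRS at weeks 2, 4, 8, 10, 14 and 18. The Power and statistical analysis section bases the sample size on the Conners' from baseline to week 18 over six time points.

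**The concern.** Week 18 is the only assessment after treatment stops. To read a change from week 14 to week 18 as an effect of stopping, everything else about the measurement has to stay the same. For the BRUMS it does not: a child's own report is followed by a parent's report, or by a joint one. Treatment status and informant change at the same moment.

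The wording about completing the scales alone or with the child covers both scales, so it also reaches the primary outcome. The CPRS is a parent report, yet at week 18 the child may take part, and by the plan's own account usually does. No rule says when, and nothing asks for it to be recorded. Because week 18 is inside the powered comparison, this looseness enters the primary model.

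**Working it through.** **1. Who answers, by visit**

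| Visit | BRUMS | CPRS |
|---|---|---|
| Baseline (week 2), weeks 8 and 14 | Child (participants do all tests; same outline at later centre visits) | Parent (Primary outcome section) |
| Weeks 4 and 10 | Child (explicit) | Parent (explicit) |
| Week 18 | Parent, alone or more usually with the child | Parent, alone or more usually with the child |

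The BRUMS column changes its named respondent between week 14 and week 18. The CPRS column does not. What is new at week 18 for the CPRS is an explicit and open option for the child to take part; no section says whether the child took part earlier.

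**2. The plan's own figure, as background**

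The sample size is not disputed. It is reproduced to show that week 18 counts in it. The inputs from the power section are f = 0.20, m = 6 time points, two groups, alpha 0.05, power 0.80. The correlation between time points is not stated; rho = 0.5 is assumed. For the between-groups test in a repeated-measures ANOVA:

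- lambda = N f² m / (1 + (m − 1) rho) = 118 × 0.04 × 6 / 3.5 = 8.09
- critical F(1, 116) = 3.92, power = 0.805
- dropout: 118 / (1 − 0.20) = 147.5, so 148, against 150 stated

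The stated 118 and 3.92 are recovered, and 150 is close. Other assumed correlations give N = 84 (rho 0.3) and N = 150 (rho 0.7). The match with m = 6 is consistent with week 18 carrying one sixth of the weight in the averaged comparison.

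**3. Effect on the within-arm change**

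Let s be the difference in mean score, in SD units, between two ways of completing the form. The documents give no value; 0.2 to 0.5 is assumed. If every BRUMS form in an arm moves from one way to the other at week 18, then

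observed change (14 to 18) = true change + s.

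The error is the whole of s, 0.2 to 0.5 SD. Without a respondent who stays the same, no analysis can separate the two terms.

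**4. Effect on the between-arm comparison at week 18**

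Let pA and pB be the shares of forms completed in one of the two ways in each arm. Then bias = s × (pA − pB).

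- Equal mix: 0
- 10 points apart: 0.2 × 0.10 = 0.02 to 0.5 × 0.10 = 0.05 SD
- 20 points apart: 0.2 × 0.20 = 0.04 to 0.5 × 0.20 = 0.10 SD

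With an equal mix p, the shift adds variance s² p(1 − p), which is at most s²/4: 0.2²/4 = 0.01 to 0.5²/4 = 0.0625 SD².

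**5. Effect on the six-point CPRS comparison**

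If the same imbalance applied to the CPRS at week 18 only, the six-point mean would move by one sixth of the bias: 0.02/6 = 0.003 to 0.10/6 = 0.017 SD. The planned difference is 2f = 2 × 0.20 = 0.40 SD for two equal groups. The effect on the primary comparison is small under these assumptions.

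**The case against.** **The trial tests against placebo, not within arms.** This stands for the treatment comparison. The trial is randomised and double-blind, so a change of respondent falls on both arms alike, and no section powers or tests a within-arm contrast from week 14 to week 18. It does not remove the point, because the follow-up section itself gives change since stopping as the purpose of the visit.

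**The CPRS rater does not change.** This also stands. A reader might infer that the week 18 CPRS is a different measurement from the other five. The documents do not support that: the parent is named at every visit, and nothing says that earlier forms were completed without the child. The remark about usual practice may describe the whole study. What remains is that the manner of completion is left open.

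**A large loss of efficiency.** A reader might try to size the harm by assuming that the week 14 to 18 correlation falls from 0.5 to 0.25. The variance of change, 2(1 − r), would rise from 1.0 to 1.5 SD², a relative efficiency of 1/1.5 = 0.67. Both correlations are invented, and the sum does not carry over to the six-point mean. With the same values, the variance of that mean goes from (6 + 30 × 0.5)/36 = 0.583 to (6 + 20 × 0.5 + 10 × 0.25)/36 = 0.514, so it does not rise. No efficiency figure should be attached to this point.

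**Age suitability.** The Mood section says that the BRUMS "was designed for purely adolescent populations", while enrolment starts at age 6. A reader might infer that parents answer at week 18 for that reason, or that younger children's mood data should be set apart. The document gives no such reason, and whether the scale suits younger children is a separate question.

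**A condensed article leaves such detail out.** This would answer an omission. Here the article states one mood respondent in the Procedure section and another in the follow-up section, and it expressly allows two modes.

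**Conclusion.** The point holds for the BRUMS. Followed as written, the mood informant changes from child to parent, usually jointly with the child, at the one visit meant to show what happens after stopping. The within-arm week 14 to 18 mood change is confounded with that switch by the full size of any difference between informants, 0.2 to 0.5 SD on the assumed range. The randomised comparison at week 18 is unbiased if the respondent mix is the same in both arms. It is off by 0.02 to 0.10 SD if the mix differs by an assumed 10 to 20 points, and otherwise mainly gains some noise.

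For the CPRS, only unstandardised child involvement at one of the six time points in the powered comparison is shown; a change of rater is not. All sizes rest on assumed values, because the documents give none. The change of named mood respondent rests on the text alone. The correction is worth making because it costs almost nothing and protects the only post-cessation assessment.

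**What to change.** Reconcile the Procedure text after Table 1, the post-treatment follow-up section and the Primary outcome section so that they state the following:

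- The child completes the BRUMS at every time point, including week 18.
- The same parent completes the CPRS at all six time points in one stated mode, with the child's involvement either excluded throughout or handled the same way throughout.
- Each form records who answered and whether anyone else took part.

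The cost is a sentence or two and one field on each form; sample size, visits and instruments are unchanged. If week 18 forms have already been collected under the current wording, report who answered where this is known, and do not interpret the within-arm week 14 to 18 mood change as an effect of stopping.
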